**Figure 2 F2:**
[figure not shown]
**Calculation of the M value.** SAQ, Seattle Assessment Questionnaire.

1.a.i. Find patients receiving treatment A (or treatment B) whose self-reported Likert scores are within the range of +2 to +3.

1.a.ii. Collect the corresponding SAQ score of these patients, use X_1_ to refer to it and calculate the mean value $X{\left(—\right)}_{1}$.

1.a.iii. Find patients receiving Treatment A (or Treatment B) whose self-reported Likert scores are within the range of 0 to +1.

1.a.iv. Collect the SAQ scores of these patients, use X_0_ to refer to it and calculate the mean value X_0_

1.a.v. $M_{0}=X_{0}-X{\left(—\right)}_{0}$

1.a.vi. $M_{1}=X_{1}-X{\left(—\right)}_{1}$

2. Calculation of SEM (SEM_0_ and SEM_1_) [7,12,13].

$$\mathrm{SEMO}=\sqrt{\sum M0^{2}/\left(n-1\right)}\times \sqrt{1-r}$$

$$\mathrm{SEM}1=\sqrt{\sum M1^{2}/\left(n-1\right)}\times \sqrt{1-r}$$

n:sample size; r:the reliability coefficient of SAQ

3. Calculation of MCID We will calculate the MCIDs for treatment A (referred to as MCID1) and treatment B (referred to as MCID2) during the first treatment period and for treatment A (referred to as MCID3) and treatment B (referred to as MCID4) during the crossover period.

MCID, Minimal clinically important difference; SEM, Standard error of measurement.

$$\mathrm{MCID}\;=\;\sqrt{\mathrm{SEM}O^{2}+\mathrm{SEM}1^{2}}$$

4. Individualized efficacy evaluation upon the first round of treatment: Treatment interventions will be defined as either effective or ineffective by comparison of the patient’s personal SAQ score with the calculated MCID value.

4.a. Treatment A will be defined as effective if a patient receiving it has a SAQ score greater than the MCID1 score.

4.b. Treatment B will be defined as effective if a patient receiving it has a SAQ score greater than the MCID2 score.

4.c. A treatment will be adjudged ineffective if a patient receiving it reports a SAQ score lower than the corresponding MCID value (MCID1 or MCID2).

5. Individualized efficacy evaluation upon crossover of treatment: Because of the complexity of the study design, all the patients will be categorized into four groups by using the following assessment tools:

5.a. Group 1: Both treatments A and B are effective for patients in this group:

5.a.i. For patients who first receive treatment A and then treatment B, the first SAQ score > MCID1 and the second SAQ score > MCID4

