5.a.ii. For patients who first receive treatment B and then treatment A, the first SAQ score > MCID2 and the second SAQ score > MCID3

5.b. Group 2: Treatment A is effective and treatment B is ineffective for patients in this group:

5.b.i. For patients who first receive treatment A and then treatment B, the first SAQ score > MCID1 and the second SAQ score < MCID4

5.b.ii. For patients who first receive treatment B and then treatment A, the first SAQ score > MCID2 and the second SAQ score < MCID3.

5.c. Group 3: Treatment B is effective and treatment A is ineffective for patients in this group:

5.c.i. For patients who first receive treatment A and then treatment B, the first SAQ score < MCID1 and the second SAQ score > MCID4

5.c.ii. For patients who first receive treatment B and then treatment A, the first SAQ score < MCID2 and the second SAQ score > MCID3

5.d. Group 4: Both treatments A and B are ineffective for patients in this group:

5.d.i. For patients who first receive treatment A and then treatment B, the first SAQ score < MCID1 and the second SAQ score < MCID4

5.d.ii. For patients who first receive treatment B and then treatment A, the first SAQ score < MCID2 and the second SAQ score < MCID3

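### For patients who take B then A, the conditions for Group 2 and Group 3 are exchanged, so discordant responders in that sequence are credited to the wrong drug

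*Protocol article*

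**What the plan says.** All the text is in the protocol article, Methods, under Efficacy assessment tools, except the table legend and the use of the counts.

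- Step 3 sets the thresholds "for treatment A (referred to as MCID1) and treatment B (referred to as MCID2) during the first treatment period". After crossover, MCID3 is the threshold for A and MCID4 the one for B.
- Step 4 gives the decision rule. For example, "Treatment B will be defined as effective if a patient receiving it has a SAQ score greater than the MCID2 score". Conversely, "A treatment will be adjudged ineffective if a patient receiving it reports a SAQ score lower than the corresponding MCID value".
- Step 5 sorts patients into four groups after crossover. The heading at 5.b is "Group 2: Treatment A is effective and treatment B is ineffective for patients in this group". The heading at 5.c states the reverse for Group 3.
- For patients who receive B first and A second, step 5.b.ii places in Group 2 those for whom "the first SAQ score > MCID2 and the second SAQ score < MCID3". Step 5.c.ii places in Group 3 those for whom "the first SAQ score < MCID2 and the second SAQ score > MCID3".
- The legend of Table 1 reads the Group 2 counts (A1 to A4) as QSYQ effective and TXL not, and the Group 3 counts (B1 to B4) as the opposite.
- Tables 1 and 2 feed the correspondence analysis. There, the distance between a symptom combination and an outcome group decides which indication is attached to which drug.

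**The concern.** A patient in the B-then-A sequence has the first score taken on B and the second on A. The inequality pattern that means A only in the A-then-B sequence therefore means B only here. Steps 5.b.ii and 5.c.ii keep the A-then-B pattern without reversing it, so they contradict both their own headings and the Table 1 legend.

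Groups 2 and 3 are the only outcome groups that separate the two drugs. Group 1 holds patients helped by both and Group 4 those helped by neither. If discordant patients from one sequence are put in the wrong group, the two columns that should tell QSYQ from TXL mix the drugs. The stated aim of finding the best indications for each drug rests on those columns.

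**Working it through.** **Inputs from the protocol.** Thresholds: MCID1 for A and MCID2 for B in period 1; MCID3 for A and MCID4 for B after crossover (step 3). A score above its threshold means effective, below it ineffective (step 4). Layout: 20 patients start on A and 20 on B in each symptom combination (Sample size calculation), so 20 + 20 = 40, which is the N in the Table 1 legend, and 4 × 40 = 160.

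**Step 1: the eight rules against their headings.**

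| Sequence | First score | Second score | Meaning by steps 3 and 4 | Printed group | Group by heading |
|---|---|---|---|---|---|
| A then B | > MCID1 | > MCID4 | both effective | 1 | 1 |
| A then B | > MCID1 | < MCID4 | A only | 2 | 2 |
| A then B | < MCID1 | > MCID4 | B only | 3 | 3 |
| A then B | < MCID1 | < MCID4 | neither | 4 | 4 |
| B then A | > MCID2 | > MCID3 | both effective | 1 | 1 |
| B then A | > MCID2 | < MCID3 | **B only** | **2** | **3** |
| B then A | < MCID2 | > MCID3 | **A only** | **3** | **2** |
| B then A | < MCID2 | < MCID3 | neither | 4 | 4 |

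Six of the eight rules agree with their headings; 5.b.ii and 5.c.ii do not. Read as printed, Group 2 collects patients for whom only the first-period drug worked, and Group 3 those for whom only the second-period drug worked, in both sequences.

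**Step 2: expected counts per symptom combination.** Let pA and pB be the shares of patients helped by A only and by B only, taken as the same in both sequences (no period or carryover effect). Let nAB and nBA be the sequence sizes.

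- Printed rules: Group 2 = nAB·pA + nBA·pB; Group 3 = nAB·pB + nBA·pA. The difference is (nAB − nBA)(pA − pB).
- Rules that follow the headings: Group 2 = (nAB + nBA)·pA; Group 3 = (nAB + nBA)·pB.

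With nAB = nBA = 20, the printed difference is (20 − 20)(pA − pB) = 0, and each group has the expected share (pA + pB)/2. With 16 and 16 after the planned 20% dropout, it is again 0.

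**Step 3: illustration.** The protocol gives no responder shares, so all of these are assumed (20:20).

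| pA | pB | Printed Group 2 v 3 | By headings Group 2 v 3 |
|---|---|---|---|
| 0.30 | 0.10 | 8 v 8 | 12 v 4 |
| 0.40 | 0.20 | 12 v 12 | 16 v 8 |
| 0.50 | 0.10 | 12 v 12 | 20 v 4 |
| 0.60 | 0 | 12 v 12 | 24 v 0 |

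For the first row:

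- Printed Group 2 is 20 × 0.30 + 20 × 0.10 = 6 + 2, so 2/8 = 25% are wrong-drug patients.
- Printed Group 3 is 20 × 0.10 + 20 × 0.30 = 2 + 6, so 6/8 = 75% are wrong-drug patients.
- Misclassified over the trial: 80 × (0.30 + 0.10) = 32 of 160, or 20%.

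**Step 4: when the conditions of step 2 fail.**

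- Unequal sequences (assumed 24:16, pA 0.30, pB 0.10): printed 24 × 0.30 + 16 × 0.10 = 8.8 v 24 × 0.10 + 16 × 0.30 = 7.2, against 12 v 4 by the headings. A diluted drug signal remains.
- Period effect and no drug difference (assumed 0.30 first drug only, 0.10 second drug only, in both sequences): printed 40 × 0.30 = 12 v 40 × 0.10 = 4. By the headings, both groups are 20 × 0.30 + 20 × 0.10 = 8. The printed rules would show a period effect as a drug difference.

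**Step 5: consequence for the correspondence analysis.** Under the conditions of step 2, the Group 2 and Group 3 columns have equal expected counts in every row of Table 1. Table 2 sums those rows, so the same holds there. The two column points then coincide in expectation, and only chance separates them in the plot.

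**The case against.** The strongest reply is that this is a drafting slip with an obvious intent. The headings at 5.b and 5.c and the Table 1 legend state the meaning of each group without ambiguity, and the A-then-B rules follow it. An analyst who works from the headings would classify every patient correctly. This stands in part: the harm depends on the printed conditions being implemented, and the article shows no program. But the numbered conditions are the only operational rules given, and nothing elsewhere corrects them. Output from them would look normal, since every patient is classified and the totals add up. A text-reading fault is unlikely, because 5.a.ii and 5.d.ii use the same thresholds in the same order correctly.

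A reader might also infer more than the text supports:

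- That all of the roughly 80 B-then-A patients are misclassified. They are not: those in Groups 1 and 4 are handled correctly, and 80 would be reached only if every one of them had discordant results.
- That half of each group consists of wrong-drug patients. That holds only if pA = pB, when there is no drug difference to lose.
- That the contrast vanishes under any circumstances. It does so only in expectation, with equal sequences and no period or carryover effect.

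**Conclusion.** The contradiction is certain and is shown by the protocol's own definitions: two of the eight classification rules stand under the wrong heading. If they are implemented as printed, every B-then-A patient with discordant results is assigned to the wrong drug. The number affected is 80 × (pA + pB), which is 32 of 160 with assumed shares of 0.30 and 0.10.

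With equal sequences and no period or carryover effect, the expected contrast between Groups 2 and 3 is zero whatever pA and pB are. With a period effect, the contrast mainly reflects that effect; with unequal sequences alone, a diluted drug signal is left.

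This must be corrected before tabulation, because these rules supply the only between-drug contrast in Tables 1 and 2 and in the correspondence analysis. It does not follow that the final analysis will be wrong, since an analyst may follow the headings instead.

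**What to change.** Exchange the two B-then-A conditions and leave everything else in step 5 unchanged:

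- 5.b.ii (Group 2): first SAQ score < MCID2 and second SAQ score > MCID3.
- 5.c.ii (Group 3): first SAQ score > MCID2 and second SAQ score < MCID3.

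All eight rules then agree with their headings and with the Table 1 legend. Check any classification program against the group headings before tabulation, for example by running the eight patterns in the table above through it. The cost is two lines of text and, where needed, the matching lines of code. No patients, visits or data are added.

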### Statistical analysis

#### *Test for baseline balance*

Baseline data will be analyzed using an independent *t*-test, analysis of variance and the *χ*^2^ test to check whether the randomization has resulted in equal distributions of known confounding factors, such as age, gender, living status and education level.

#### *Comparison of the curative effects of treatment A and treatment B on symptoms related to angina*

Table 1 shows how the intervention treatments work for patients presenting with each of the four symptom combinations.

**Table 1 T1:** Efficacy assessment by category of single symptom combination

**Type of symptom combination**	**Four groups of patients categorized using the efficacy assessment tool**			
	**Group 1**	**Group 2**	**Group 3**	**Group 4**
Combination 1	AB1/*N*	A1/*N*	B1/*N*	ab1/*N*
Combination 2	AB2/*N*	A2/*N*	B2/*N*	ab2/*N*
Combination 3	AB3/*N*	A3/*N*	B3/*N*	ab3/*N*
Combination 4	AB4/*N*	A4/*N*	B4/*N*	ab4/*N*

AB1 to AB4 refer to the number of patients requiring treatment for symptom combinations 1 to 4 and for whom both QSYQ and TXL are effective. A1 to A4 refer to the number of patients requiring treatment for symptom combinations 1 to 4 and for whom QSYQ is effective and TXL is ineffective. B1 to B4 refer to the number of patients requiring treatment for symptom combinations 1 to 4 and for whom QSYQ is ineffective and TXL is effective. ab1 to ab4 refer to the number of patients requiring treatment for symptom combinations 1 to 4 and for whom both QSYQ and TXL are ineffective *N* refers to the total number of patients who fall within each symptom combination group, which is planned to be 40.

Table 2 shows how the intervention treatments will work for patients presenting with two or more of the four symptom combinations. All possible symptom combinations are presented in the table. The total number of patients acting as the denominator increases with the number of symptom combinations involved.

**Table 2 T2:** Efficacy assessment by category of multiple symptom combinations

**Multiple symptom combinations**	**Four groups of patients categorized using the efficacy assessment tool**			
	**Group 1**	**Group 2**	**Group 3**	**Group 4**
Combination (1 + 2)	(AB1 + AB2)/2 *N*	(A1 + A2)/2 *N*	(B1 + B2)/2 *N*	(ab1 + ab2)/2 *N*
Combination (1 + 3)	(AB1 + AB3)/2 *N*	(A1 + A3)/2 *N*	(B1 + B3)/2 *N*	(ab1 + ab3)/2 *N*
Combination (1 + 4)	(AB1 + AB4)/2 *N*	(A1 + A4)/2 *N*	(B1 + B4)/2 *N*	(ab1 + ab4)/2 *N*
Combination (2 + 3)	(AB2 + AB3)/2 *N*	(A2 + A3)/2 *N*	(B2 + B3)/2 *N*	(ab2 + ab3)/2 *N*
Combination (2 + 4)	(AB2 + AB4)/2 *N*	(A2 + A4)/2 *N*	(B2 + B4)/2 *N*	(ab2 + ab4)/2 *N*
Combination (3 + 4)	(AB3 + AB4)/2 *N*	(A3 + A4)/2 *N*	(B3 + B4)/2 *N*	(ab3 + ab4)/2 *N*
Combination (1 + 2 + 3)	(AB1 + AB2 + AB3)/3 *N*	(A1 + A2 + A3)/3 *N*	(B1 + B2 + B3)/3 *N*	(ab1 + ab2 + ab3)/3 *N*
Combination (1 + 2 + 4)	(AB1 + AB2 + AB4)/3 *N*	(A1 + A2 + A4)/3 *N*	(B1 + B2 + B4)/3 *N*	(ab1 + ab2 + ab4)/2 *N*
Combination (1 + 3 + 4)	(AB1 + AB3 + AB4)/3 *N*	(A1 + A3 + A4)/3 *N*	(B1 + B3 + B4)/3 *N*	(ab1 + ab3 + ab4)/3 *N*
Combination (2 + 3 + 4)	(AB2 + AB3 + AB4)/3 *N*	(A2 + A3 + A4)/3 *N*	(B2 + B3 + B4)/3 *N*	(ab2 + ab3 + ab4)/3 *N*
Combination (1 + 2 + 3 + 4)	(AB1 + AB2 + AB3 + AB4)/4 *N*	(A1 + A2 + A3 + A4)/4 *N*	(B1 + B2 + B3 + B4)/4 *N*	(ab1 + ab2 + ab3 + ab4)/4 *N*

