## Objectives

We are conducting a multicenter, randomized, controlled, double-blind, double-dummy clinical trial to compare the effectiveness of two Chinese patent medicines for angina patients diagnosed with qi deficiency and blood stasis syndrome. The ultimate goal is to test the proposed methodology for the individualized evaluation of the therapeutic effects of Chinese patent drugs and for distinguishing between drugs targeting a multitude of similar indications.

To fulfill these objectives in our present study, we highlight the introduction of trial participants’ therapeutic needs and willingness in terms of group allocation and the use of CER methodology. Specifically before being entered into the randomization process, all eligible participants with qi deficiency and blood stasis syndrome will first be allowed to choose from among four prespecified groups of symptoms which they would most like to be addressed. The outcomes for these symptoms are considered PIOs and will be assessed using PRO instruments. Furthermore, we will test the use of the CER method to compare the curative effects of QSYQ dripping pills and TXL capsules, two widely used Chinese patent medicines for angina patients with qi deficiency and blood stasis syndrome. By analyzing and comparing the effects of the two drugs for each symptom group, we aim to summarize the characteristics of the drugs’ curative effects and identify the best targeted indications for each drug.

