### Correspondence analysis

Correspondence analysis (CA) is a statistical technique designed to demonstrate or summarize a set of data in two-dimensional graphical form, typically a biplot, which can help in the detection of the structural relationships among the variables contained in the rows and columns of a contingency table. In this study, SPSS version 16.0 software (SPSS Inc, Chicago, IL, USA) will be used to perform CA of the data in Tables 1 and 2. Statistical analysis will follow the steps listed below:

1. Specify the value of dimensions.

2. For both tables, the number of dimensions will be set at two.

3. Production of a CA plot.

The biplot is a matrix of joint plots of the row and column points. In the biplot, types of symptom combinations and different outcome groups are shown as points. The abscissa value is determined by the score of the first dimension of symptom combinations and outcome groups. The ordinate value is the score of the second dimension of symptom combinations and outcome groups.

4. Calculation of “D (A–B)” refers to the relative distance between point A and point B in the biplot. “a1” and “b1” refer to the abscissa values of point A and point B. “a2” and “b2” refer to the ordinate values of point A and point B.

5. The relative distance between points displayed in the CA plot will be summarized in a table. As prespecified, the pair of symptom combinations and outcome types with the nearest relative distance will signify the most significant correlation. The characteristic indications for which the patent drug is most effective will be found upon careful screening.

6. The value of relative distance between two points in the biplot will be calculated using the following formula.

$$D\left(A‒B\right)=\sqrt{{\left(a1\;‒\;b1\right)}^{2}+{\left(a2-b2\right)}^{2}}$$

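### The plan aims to name each drug's most effective indication, but no table, rule or plot point gives a drug's success rate: successes are split over joint outcome groups and never added

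*Protocol article*

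**What the plan says.** The Objectives section states a per-drug aim: to "identify the best targeted indications for each drug". Step 5 of the Correspondence analysis section repeats it: "The characteristic indications for which the patent drug is most effective will be found upon careful screening".

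The data for that step come from Tables 1 and 2, whose columns are headed "Four groups of patients categorized using the efficacy assessment tool". The four groups exclude one another:

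- Group 1 (AB): patients "for whom both QSYQ and TXL are effective"
- Group 2 (A): patients "for whom QSYQ is effective and TXL is ineffective"
- Group 3 (B): patients "for whom QSYQ is ineffective and TXL is effective"
- Group 4 (ab): patients in whom neither drug works

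The denominator N for each symptom combination is the group size, "which is planned to be 40". Table 2 adds cells, but only across symptom combinations within one outcome group: "The total number of patients acting as the denominator increases with the number of symptom combinations involved". It never adds Group 1 to Group 2, or Group 1 to Group 3.

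The correspondence analysis is run on these two tables in two dimensions. The closest pair of a symptom combination and an outcome group is taken as the strongest link. All four outcome groups are points in the plot. The text does not say which of them are to be read for QSYQ and which for TXL. Under Efficacy assessment tools, item 4 defines success on a single drug after the first period, but no table carries that definition forward.

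**The concern.** Where a drug is most effective is a question about that drug's own success rate. Under this design that rate is a sum of two columns: both-effective plus QSYQ-only for QSYQ, and both-effective plus TXL-only for TXL. The plan keeps the columns apart and turns each into its own point. Group 1 is shared by the two drugs and leaves out part of each drug's successes. Groups 2 and 3 are the only points specific to a drug, and each also requires the other drug to fail. Nearness to any one point is therefore not a measure of how often a drug works.

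The statement of each drug's best indication is the trial's main product. If it is taken from a single-drug point, a combination with a modest success rate can be named and the one with the highest rate passed over.

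**Working it through.** **1. Algebra on the Table 1 cells.** For combination k with n patients:

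- QSYQ success rate = (ABk + Ak)/n
- TXL success rate = (ABk + Bk)/n
- Group 2 share = Ak/n = QSYQ success rate − ABk/n
- Difference between drugs = (ABk + Ak)/n − (ABk + Bk)/n = (Ak − Bk)/n

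At a fixed QSYQ success rate, the Group 2 share falls one for one as more of those patients also respond to TXL. It is not a measure of QSYQ's effectiveness. The last line shows that Groups 2 and 3 are the right cells for comparing the drugs.

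**2. Assumed example.** The protocol gives no response rates, so the counts are invented, with 40 per combination as in Table 1. Distances use the protocol's formula, D = √[(a1 − b1)² + (a2 − b2)²], on a two-dimensional correspondence analysis with symmetric normalisation (also an assumption).

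| Combination | Groups 1/2/3/4 | QSYQ effective | TXL effective | (A − B)/40 | D to Group 1 | D to Group 2 | D to Group 3 |
|---|---|---|---|---|---|---|---|
| 1 | 28/4/4/4 | 32/40 = 80% | 32/40 = 80% | 0 | 0.238 | 1.627 | 1.734 |
| 2 | 4/14/4/18 | 18/40 = 45% | 8/40 = 20% | +25 points | 1.824 | 0.327 | 1.722 |
| 3 | 14/8/8/10 | 22/40 = 55% | 22/40 = 55% | 0 | 0.926 | 0.795 | 0.875 |
| 4 | 12/6/12/10 | 18/40 = 45% | 24/40 = 60% | −15 points | 1.278 | 1.223 | 0.294 |

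Combination 1 is best for both drugs. It is the farthest from Group 2 and from Group 3, and its nearest point is Group 1. Group 2 is nearest combination 2, where QSYQ works in 45%. Group 3 is nearest combination 4, where TXL works in 60%.

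**3. Dependence on scaling.** Under symmetric, principal, row-principal and column-principal normalisation alike, combination 1 is the farthest from Group 2. The nearest is combination 2 in three of them and combination 3 (55%) in column-principal. The combination named can change with scaling. Passing over the best one does not.

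**4. Simulation.** Assumptions: 5,000 trials per scenario, 32 completers per combination (40 × 0.8, from the 20% dropout in the sample size section), bivariate normal responses with within-patient correlation 0.5, symmetric normalisation.

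- Scenario 1, both drugs at 80/65/50/35%: the 80% combination is nearest Group 2 in 5% of trials, the 50% combination in 46%.
- Scenario 2, QSYQ 80% and TXL 70% in combination 1, QSYQ 50% and TXL 30% in combination 2, 50% for both elsewhere: combination 1 is nearest Group 2 in about 7%, combination 2 in 59%.
- In the same trials the nearest outcome point to the 80% combination is Group 1 in 96% (scenario 1) and 95% (scenario 2).
- The summed rate (AB + A)/n ranks the truly best QSYQ combination first in 93% and 99%, ties counted as correct.

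**5. The group labels.** Under Efficacy assessment tools, items 5.b.ii and 5.c.ii cover patients who take B first and A second. Item 5.b.ii, under the label A effective and B ineffective, requires the first score (on B) above its threshold and the second (on A) below. That is the opposite of its label, and 5.c.ii is reversed in the same way. Suppose 10 patients truly respond to A only and 4 to B only, each split evenly by sequence. Coding as written gives Group 2 = 5 + 2 = 7 and Group 3 = 2 + 5 = 7. Until this is reconciled, Group 1 + Group 2 is not the number of QSYQ successes.

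**The case against.** A reader might infer that the plan reads each drug's indication from patients in whom the other drug failed. The document does not say so. Its rule takes the closest pair over all four outcome points, Group 1 included, and then leaves the choice to screening. In the example the closest of all 16 pairs is combination 1 with Group 1 (0.24, against 0.33 for combination 2 with Group 2). The stated rule therefore shows the 80% combination as one where both drugs work, which is true of those data. This objection stands: the figures for Group 2 describe one possible reading, not a stated one.

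Groups 2 and 3 are also legitimate for the other stated aim, telling the two drugs apart. Combination 2, at +25 points, is the right answer to where QSYQ is preferable to TXL, and in scenario 1 there is no such combination to find. This too stands.

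Nothing is lost from the data either: each drug's rate is the sum of two cells in one row of Table 1. That is why the remedy is cheap, but no stated step makes the sum.

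Finally, an article may leave derived summaries to the full protocol or analysis plan. That carries less weight here, because the article prints the tables, the distance formula and the rule, and none of them addresses the per-drug quantity named in the aim. Nor does Group 1 fill the gap. It cannot separate the drugs, and it omits the successes in Groups 2 and 3.

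**Conclusion.** The concern holds as a mismatch between aim and analysis. The aim is each drug's most effective indication, yet no table, rule or plot point gives a drug's success rate, and the reading rule does not say which outcome points count for which drug. If Group 2 or Group 3 is read, the best combination can be passed over: 80% success at distance 1.63 against 45% at 0.33 in the example. The algebra needs no assumption. The sizes rest on invented counts and response rates, a correlation of 0.5 and a chosen normalisation, so they show what can happen and not how often it will.

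The documents do not support saying that the plan has committed itself to the wrong quantity, or that the comparison between the drugs is invalid. In a study that calls itself exploratory this is a worthwhile, inexpensive correction. It is not a defect that undermines the trial.

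**What to change.** 1. First reconcile items 5.b.ii and 5.c.ii under Efficacy assessment tools with their group labels, so that the columns mean what Table 1 says.
2. Add two columns to Table 1 for each combination: QSYQ effective = (AB + A)/n and TXL effective = (AB + B)/n, each with a 95% confidence interval. Take the most effective indication for each drug from these rates.
3. Keep Group 2 against Group 3, that is A − B, for the question of one drug rather than the other.
4. Reword step 5 of the Correspondence analysis section so that nearness in the plot is descriptive and is not read as where a drug is most effective.

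The cost is two derived columns and one sentence, besides reconciling the two items. No new data are needed, and the design and sample size are untouched.

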### Patient grouping and treatment allocation

Using stratified and blocked randomization, we will first categorize eligible participants into four groups on the basis of their varied choice of secondary symptoms to be addressed, and then we will randomly assign them to one of the two treatment arms at a ratio of 1:1. To minimize imbalances across groups, gender will also be used as a stratification factor. The random number sequence will be generated by a third-party statistician using SAS version 9.1 software (SAS Institute, Cary, NC, USA).

The four symptom combination groups, each representing the signs a patient most wishes to bring under control, were formed according to the characteristic physical manifestations of the qi deficiency and blood stasis syndrome defined in the 2002 Guidelines for Clinical Research of Chinese Medicine (new drug). The grouping criteria for patients with varying therapeutic needs resulted in the following four symptom combination groups:

1. Combination 1: chest pain + chest tightness + shortness of breath

2. Combination 2: chest pain + chest tightness + fatigue

3. Combination 3: chest pain + chest tightness + palpitations

4. Combination 4: chest pain + chest tightness + spontaneous perspiration

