### Sample size calculation

Sample size estimation is based on the results of a pilot study that showed the difference in changes in Seattle Angina Questionnaire (SAQ) scores of 2 ± 2.5 between the group receiving QSYQ dripping pills and the group taking TXL capsules. Assuming a two-sided *P*-value of 0.05, 90% power and calculating for a dropout rate of 20%, one would need to have approximately 160 patients with 80 in each treatment group. We used the PAST software program to calculate these statistics (http://folk.uio.no/ohammer/past/) [10]. Therefore, we plan to recruit 40 patients for each of the four symptom combinations, from among whom 20 will be assigned to treatment arm A (QSYQ) and 20 to treatment arm B (TXL). In all, 160 patients will be recruited.

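### Tables 1 and 2 divide by the recruited number per symptom combination, but only patients with both period scores can be placed in Groups 1 to 4, so rows sum to about 0.80 at the planned dropout

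*Protocol article*

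**What the plan says.** Under Sample size calculation, the protocol article arrives at 160 patients, "calculating for a dropout rate of 20" per cent, and continues: "we plan to recruit 40 patients for each of the four symptom combinations", 20 to each treatment arm.

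Under Efficacy assessment tools, step 5 states that "all the patients will be categorized into four groups by using the following assessment tools". Each rule joins a condition on the first-period score to one on the second-period score. For patients who take A and then B, for example, Group 4 requires "the first SAQ score < MCID1 and the second SAQ score < MCID4". No rule covers a patient without a second score. Step 4 separately judges each patient effective or ineffective after the first period alone.

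Under Comparison of the curative effects, Table 1 divides the count in each group by N, which "refers to the total number of patients who fall within each symptom combination group, which is planned to be 40". Table 2 pools combinations and divides by 2N, 3N or 4N. Under Correspondence analysis, both tables feed the biplot, and the nearest distance between a combination and an outcome group is taken as the strongest association.

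**The concern.** The denominator and the numerators cover different patients. A patient belongs to a combination by choosing symptoms before randomisation, so N includes those who later leave. The numerators can include only patients who reach the end of the second treatment period, after 28 + 10 + 28 = 66 days.

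The printed proportions therefore mix response with completion of the schedule. The trial aims to find the symptom combination for which each drug works best. If dropout differs between combinations, the rates will differ even where response among completers is the same. Separately, if patients leave because one drug failed them, failures on that drug are missing from the table.

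**Working it through.** **Inputs.** From Sample size calculation: 160 recruited, 40 per combination, 20% dropout. From the Table 1 note: N planned to be 40. From step 5: both scores are needed for classification.

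**The plan's own figure.** 160 / 4 = 40 = 20 + 20, so the planned N equals the number recruited per combination. The 160 itself does not follow from the stated inputs. With difference 2, SD 2.5, two-sided 0.05 and 90% power, 2 × (1.960 + 1.282)² × (2.5/2)² = 32.8, or 33 per arm. Then 33/0.8 gives 42 per arm, 84 in total. That is a separate matter. The present point uses only the statement that the 160 includes the dropout allowance.

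**Row sums.** Classified per combination = 40 × (1 − d). Printed proportion = proportion among classified × (1 − d).

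| Dropout d | Classified of 40 | Row sum | 50% prints as | 20% in Group 4 prints as |
|---|---|---|---|---|
| 10% (assumed) | 36 | 0.90 | 45% | 18% |
| 20% (protocol) | 32 | 0.80 | 40% | 16% |
| 30% (assumed) | 28 | 0.70 | 35% | 14% |

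In Table 2 the planned denominators 80, 120 and 160 would hold 64, 96 and 128 classified patients, again a factor of 0.80.

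**Neither convention.** Take a Group 4 rate of 20% among completers at 20% dropout: 0.20 × 32 = 6.4 patients. As written, the table prints 6.4/40 = 16%. A completer analysis gives 6.4/32 = 20%. Counting the 8 dropouts as failures of both drugs gives (6.4 + 8)/40 = 36%.

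**Comparison of drugs within a row.** The factor (1 − d) applies to all four cells, so the ratio of A-only to B-only does not change.

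**Correspondence analysis.** The method starts from each cell divided by the grand total, so a common N cancels. A check on an invented Table 1 with 38, 34, 30 and 26 completers gave the same distances from the counts and from counts/40 (difference below 1e-14). Replacing N by another common value in Table 2 also changes nothing.

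Dividing each row by its own completers does change the result, because it gives all rows equal weight. In the same invented table, the combination nearest Group 1 was combination 3 on counts (0.467, against 0.554 for combination 4). On completer proportions it was combination 4 (0.466, against 0.524 for combination 3).

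**Dropout related to failure (assumed illustration).** Take 40 patients, truly 10 in each group by the group headings, of whom 8 leave because A fails: 4 from Group 3 (B only) and 4 from Group 4. The table then holds 10, 10, 6 and 6. A-only against B-only reads 10 to 6, although the truth is 10 to 10. Over 40 this is 25% against 15%. Over 32 it is 31.25% against 18.75%. The ratio is equally wrong with either denominator.

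**The case against.** The strongest reply is that 40 is only a planned value, so N may be the actual number at analysis, and that an article leaves analysis sets to a fuller document. In part this stands: the text does not say outright whether N means recruited or classified. But N is defined by membership of a combination, which is settled before randomisation. Table 2 also uses multiples of one common N, which does not fit completer numbers that vary by row. This is a stated rule that conflicts with the stated classification, not just an omitted detail.

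A second reply is that dividing by all randomised patients is a legitimate convention. For Groups 1 to 3 it amounts to counting dropouts as not effective. Those patients would then have to appear in Group 4, and no rule puts them there.

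A reader might infer that the denominator understates the drugs' effective rates in particular and so biases the comparison between them. The documents do not support that: the ineffective column shrinks by the same factor. A reader might also infer that the correspondence analysis is spoiled by dividing by 40. It is not, even when dropout differs between combinations. Nor is the first-period information of non-completers thrown away altogether, since step 4 evaluates it; Tables 1 and 2 just do not carry it.

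**Conclusion.** The point holds as a defect in the printed proportions and is worth correcting. At the protocol's own 20% dropout, rows sum to 0.80 and every cell is 20% lower in relative terms than its rate among classified patients. This assumes N is applied as the number recruited and that dropouts lack a second score.

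Differences between combinations depend on how unevenly patients drop out, on which the protocol gives no figure. With assumed dropout of 10% and 30%, the same 50% would print as 45% and 35%, a gap of 10 points with no difference in response among completers. The common divisor leaves the within-row drug ratios and the correspondence analysis unchanged. Dropout that follows failure on one drug can distort both, but it acts through the need for two scores, and its size cannot be judged from the protocol.

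**What to change.** - In Tables 1 and 2, use as denominator each combination's actual number classified in both periods. In Table 2, use sums of these numbers instead of 2N, 3N and 4N. This also removes an inconsistency in the row for combinations 1 + 2 + 4, where the Group 4 cell is divided by 2N and the other three by 3N.
- Add a column for patients who cannot be classified, by sequence and by the drug taken when they left.
- Run the correspondence analysis on the counts, so that the new denominators do not alter its row weights. For Table 1 this equals the analysis with a common N. For Table 2 it does not quite, because the multipliers 2, 3 and 4 differ between rows; on counts, larger pools weigh more, and the text should say so.
- Beside the tables, report the step 4 first-period effective rate per drug over all randomised patients of each combination, with dropouts counted as not effective as a sensitivity analysis. The new denominator does not deal with dropout related to failure; this report and the column of unclassified patients make it visible.

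The cost is revised table notes, one added table and smaller stated denominators (about 32 instead of 40). No new data are needed.
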